### Recruitment, randomization, and assignment of intervention

2.6

Gate keepers at the Berlin governing structures responsible for kindergartens, contact leads from cooperative partners in Berlin will identify interested kindergartens. Members of the study team (SB – experienced scientific researcher, study coordination, AT – study administration) will contact these via email in which a flyer about the project will be included as additional information. Once interested, kindergartens will be contacted via telephone and site feasibility will be assessed for inclusion.

After being recruited to the study, kindergartens with a similar socio-economic level will be match-paired according to statistical demographic analysis of locations in Berlin (14).

The kindergartens will then be randomized within their matched pair to either the intervention or the waitlist group using the randomizing function of Python 3.10.6, executed by an experienced biostatistician (FK). The allocated study group will not be blinded, as this would not be possible due to the nature of the interventions. Therefore, the kindergartens, caregivers and children will be aware whether they are in the Kneipp or in the waitlist group.

### Data collection and management

2.7

The study will be conducted with two-time measurement periods, each 6 weeks long, whereby caregivers will complete an online questionnaire via online survey based on the CCQ and the NCI-CTCAE Scales describing gastroenterological-based symptoms at the end of each week of the data collection period.

At the beginning of each measurement period, caregivers will be asked to complete an initial onboarding questionnaire containing socioeconomic background information about the family. The first measurement period will be planned in autumn 2022, followed by a second measurement in the autumn of 2023 (see Figure 3: Data Collection Flowchart).

**Figure 3 fig3:**
[figure not shown]
Data collection flowchart.

All teachers and caregivers will be informed about the purpose and implementation of the data collection as part of the evaluation via printed information sheets. The educator’s and parent’s written consent to participate will be collected (on paper) by the kindergarten directors. The following data will be recorded: Name, gender, date of birth, email, telephone number. Consents will be filed in a project folder and stored in a lockable office belonging to the kindergarten directors. The folders will be periodically checked during site visits by the study team (SB, MG – medical doctoral student, study coordination).

Focused ethnographies will be planned with the kindergarten staff to ensure that visits coincide with planned interventions. Based on these visits, willing staff will be asked to participate in a separately scheduled expert interview. Interviews will be audio-recorded, auto-transcribed via f4x (audiotranskription.de), corrected and pseudonymized. Transcripts and observation protocols will be uploaded and analyzed on a single computer with the qualitative analysis software MAXQDA 24 (Release 24.2.0).

At the beginning of the study, the study coordinator (SB) will create an electronic folder with a pseudonym for each participating kindergarten on a secure server. Documentation files with the following data will be stored in this folder:

– Main target parameters (missed days because of an infection)– Secondary target parameters (CCQ)– Interview audio and transcripts– Interview and observation field notes.

All results will be analyzed through anonymous aggregated data (quantitative part) or with the use of pseudonyms (qualitative part).

All collected study data will be collected and handled conforming to the Berlin Data protection Law (Berliner Datenschutzgesetz – BlnDSG) and in adherence with the Declaration of Helsinki code of ethics. The files will be stored in their anonymized and/or pseudonymized form after completion of the study on a Charité server for 10 years. Within the electronic survey system (SoSci), the participants are encrypted using IDs and are therefore not identifiable. The study coordinator (SB) will store the encryption list and will keep it in a locked cabinet. Access to the collected data will be restricted to members of the study team (SB, AT, MG, MB, GS, SW).

The onboarding and weekly questionnaires will be sent using the collected parent emails using the Charité version of the software SoSci (Program-Version 3.5.00).

After an initial invitation, caregivers who have not completed the survey will be reminded to complete it on a weekly basis over 6 weeks. Additionally, a study assistant (AT) will contact caregivers of missing entries via telephone. In addition to the online entries, the missed kindergarten days will be documented by the kindergarten facilities and likewise measured at the two time points for 6 weeks at baseline and 12 months after baseline.

The total number of kindergarten educator sick days will also be documented without descriptive personal data and kindergartens will report the used interventions weekly to the study assistant.

### Statistical methods

2.8

The study will be published in a peer-reviewed academic journal. Analyses of data will be performed after the collection is finalized according to the following hypotheses:

Primary Efficacy Hypothesis (Infection days leading to absence):Primary Null Hypothesis (H0): Implementation of a child-friendly Kneipp concept in the kindergartens does not lead to a significant reduction in infection-related absenteeism, after 12 months.Alternative Hypothesis (H1): Implementation of child-friendly Kneipp concept in the kindergartens results in a significant reduction in infection-related absenteeism, after 12 months.

Participant characteristics, stratified by groups (Kneipp vs. Control) will be presented. For continuous variables, descriptive statistics such as mean, standard deviation, and range will be calculated, while frequencies and percentages will be used for categorical variables.

The primary outcome will be the number of sick days reported to the kindergarten. To account for the expected overdispersion (right-skewed data because of high zero counts) in the count data, we will employ a negative binomial regression model. This model will include the group (Kneipp vs. Control) and the number of sick days at baseline as predictors. We will integrate unique kindergarten identifiers to determine if cluster effects exist.

For secondary outcome analysis, we will conduct an independent t-tests to compare the mean Common Cold Questionnaire (CCQ) scores between the Kneipp and Control groups. To investigate the interaction effects of group and sex, and group and age on CCQ scores, a two-way ANOVA will be performed. This model will include the main effects of group, sex, and age, as well as their interactions. If significant interactions are identified, post-hoc analyses will be conducted. Correlation analysis will involve calculating Spearman’s correlation coefficients to assess the relationships between CCQ scores and the number of sick days, and between CCQ scores and age. The correlation (ρ) will be interpreted based on conventional guidelines. To compare the frequencies of health outcomes such as colds, bronchitis, lung inflammation, antibiotic use, and gastrointestinal infections between the Kneipp and Control groups, chi-square tests will be performed. If the assumptions of the chi-square test are violated due to expected frequencies being less than 5, Fisher’s exact test will be used instead.

The compliance analysis will be conducted by considering both the Intention-to-Treat (ITT) and Per-Protocol (PP) populations. The ITT population will include all children from whom kindergarten reports are available. The PP population will consist of children who strictly followed the prescribed treatment and for whom complete data is available.

For handling missing data in the ITT approach, multiple imputation will be used. Sensitivity analyses will also be performed to compare the results from the ITT and PP approaches to ensure robustness of the findings.

To ensure the validity of our model assumptions, normality of the data distribution for continuous outcomes will be assessed using the Shapiro–Wilk test. If necessary, data will be transformed using appropriate methods, such as log transformation, to meet the assumptions on the statistical tests. All analysis will be considered significant if *p* < 0.05 and will be conducted using R in its current version.

Qualitative data, focused ethnography observation protocols and interview transcripts, will be analyzed with content analysis with a combined deductive and inductive analysis (18).

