**Methods and design:**

The Kita Kneipp Study, registered with the German Clinical Trial Register (DRKS-ID: DRKS00029275), is a confirmatory, mixed-method, two-armed, waitlist, clinical, cluster randomized controlled trial (RCT). Kindergartens in Berlin, Germany that would like to implement the Kneipp concept into their facility will be recruited and randomized to the intervention or control group. Changes in the number of kindergarten sick days will be the primary outcome measure. Kindergarten attendance and reason for absence including illness will be collected on a weekly basis at two time points for 6 weeks from the parents and kindergarten directors: baseline and 1 year after baseline. Secondary outcomes will measure cold symptoms through the Common Cold Questionnaire (CCQ) and National Cancer Institute – Common Terminology Criteria for Adverse Events (NCI-CTCAE) Scales describing gastroenterological-based symptoms Kindergarten educator sick days will be aggregately reported for the same time period. Kneipp concept activities will be recorded on a weekly basis over the one-year intervention period. To understand the experience of Kneipp concept implementation and possible changes in the kindergarten, expert interviews will be conducted with intervention kindergarten educators and focused ethnographies will be planned to observe and analyze the intervention activities.

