### Study setting

2.1

Prior to study data collection, the study team interviewed already-certified kindergarten directors to find out aspects of the Kneipp concept that worked well in the kindergarten setting or were potentially problematic. This expert input was used to adapt our study design to the recruited facilities.

Kindergartens that had interest in becoming certified as Kneipp kindergartens and whose personnel wanted to take part in an applied Kneipp training for kindergartens were to be recruited to the study through contacts at the Berlin Senate level who have access to a network of Berlin kindergartens. A requirement for participation is the willingness of the facilities to be randomized. Further, inclusion criteria stipulated that the kindergarten facilities be compatible for Kneipp interventions, for example that they had suitable shower facilities, outdoor spaces, and room for indoor exercise (12). Included kindergartens will be recruited in Berlin, Germany. Informational evenings are to be held with kindergarten directors, caregivers and personnel to inform about the project, and to answer questions about the study purposes, design, data protection and inclusion. Written consent for participation in the study is required from all caregivers and educators.

The study will be conducted with two-time measurement periods, each 6 weeks long. Parents will complete an online at the end of each week of the data collection period. At the beginning of each measurement period, parents will be asked to complete an initial onboarding questionnaire containing socioeconomic background information about the family. The first measurement period will be planned in autumn 2022, followed by a second measurement in the autumn of 2023. Kindergarten directors will also be asked to record absences and reasons for absence of the participating children and educators and report them after completion of each 6-week data collection period.

The quantitative data of the study will evaluate the number of sick days and symptoms for children aged 2–6 years in kindergartens that implement kindergarten-appropriate, Kneipp applications, compared to the kindergartens in the waitlist group.

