## Discussion

3

To our knowledge, this planned study is the first of its kind to specifically investigate the effects of a Kneipp intervention in kindergarten facilities. As a low-cost measure with some indicated potential to improve the health of children (8, 9), this confirmatory, mixed-method, two-armed, waitlist, clinical, cluster-RCT study shows promise for presenting evidence of a Kneipp intervention within a daycare setting. A prior RCT study about hydrotherapy in children aged 3–7 years old (intervention group – hydrotherapy and saline inhalation, control group - saline inhalation), without the holistic aspect of Kneipp found no significant results regarding incidence of colds and average duration of cold episodes (19). Seeing if a broad health-promoting concept such as Kneipp would be more beneficial is of interest. In addition to the primary and secondary outcomes the qualitative documentation has the potential to not only track the effects but also to describe how the intervention is conducted with the children and perceived by the educators. That would help recognize and evaluate possible challenges and potentials of applying such a holistic approach in childcare facilities.

Several limitations to this confirmatory study design can be considered. The pre-selection based on socio-demographic information and cluster grouping of the kindergartens to be randomized may introduce some allocation bias into the randomization process. Further, the study primary and secondary outcomes rely on self-reported measures of data gathering on the part of parents and kindergarten directors. The open-label study design could influence the subjective experience of the cold and sickness symptoms and how they report or attend kindergarten. Caregivers may show some response bias, as they are informed of the purposes of the Kneipp concept. Nevertheless, the primary measure will be double recorded by caregivers and kindergarten directors to achieve a closer approximation for internal validity. Further, the CCQ relies on the recall of symptoms by caregivers that could be affected over time. For minimizing this limitation, caregivers will be prompted to fill out the form on a weekly basis and a member of the study group (AT) will monitor the responses and, if needed, a reminder e-mail will be sent.

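### Double recording of sick days is offered as a validity safeguard, but section 2.8 ties the primary count and the ITT set to the kindergarten report and states no analysis of the caregivers' absence count

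*Protocol article*

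**What the plan says.** Two records of the same measure are collected. The Abstract says that attendance and reason for absence "will be collected on a weekly basis at two time points for 6 weeks from the parents and kindergarten directors". Section 2.7 (Data collection and management) describes the facility record as running alongside the caregivers' survey: "In addition to the online entries, the missed kindergarten days will be documented by the kindergarten facilities". It also provides weekly reminders to caregivers and telephone follow-up of missing entries.

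The Discussion (section 3) lists self-report, open-label reporting and caregiver response bias as limitations. It then gives the safeguard for the primary measure: "the primary measure will be double recorded by caregivers and kindergarten directors to achieve a closer approximation for internal validity".

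Section 2.8 (Statistical methods) fixes the analysis:

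- Source of the outcome: "The primary outcome will be the number of sick days reported to the kindergarten".
- Analysis set: "The ITT population will include all children from whom kindergarten reports are available".
- Missing data: "For handling missing data in the ITT approach, multiple imputation will be used". The variables in the imputation model are not listed.
- Primary model: negative binomial, with group and baseline sick days as predictors, and kindergarten identifiers to look for cluster effects.
- Robustness: a comparison of the ITT and per-protocol results.

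Section 2.4 (Outcomes) defines the primary outcome as days absent through illness without naming a source, so the choice of source rests on section 2.8.

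**The concern.** The article claims a property for the design in one section and does not provide for it in another. A second record supports validity only if it is compared with the first, substituted for it in a sensitivity analysis, or used where the first is missing. Section 2.8 states none of these.

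Two things are at stake. First, ITT membership depends on a document that someone at the site must return after randomization. If a director returns nothing, every child in that kindergarten falls outside the ITT set. Because kindergartens are randomized within matched pairs, that pair is then broken. The caregivers' counts for those children may be on file and would not be used. Second, the analysed count comes from facilities that know their allocation (section 2.6). If counting differed by arm, the difference would pass straight into the estimated group effect, and no stated analysis would show it.

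**Working it through.** The plan gives no figure on this point, and the sample size of 240 children is not affected by it. The check is a comparison of sections, plus one illustration.

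**1. Where caregiver data enter section 2.8.** They enter through the CCQ scores (t-tests, ANOVA, Spearman correlations). The frequencies of colds, bronchitis, lung inflammation, antibiotic use and gastrointestinal infections appear to be a further use. These are symptom scores and health events, not absence days. The nearest item is the correlation of CCQ score with number of sick days, which relates a symptom score to absence and does not compare two counts of absence. No agreement check, rule for discrepancies or model on the caregiver absence count is stated.

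**2. Who is in the ITT set.** The rule requires a kindergarten report but does not say for which period.

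| Child's data | Reports needed at both periods | One report suffices |
|---|---|---|
| Kindergarten report at both periods | in | in |
| Kindergarten report at baseline only, caregiver counts at both | out | in, follow-up count imputed |
| No kindergarten report, caregiver counts at both | out | out |

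The last row is out on either reading. Imputation within the ITT set cannot bring that child back, whatever variables it uses. On the stricter reading the middle row is lost as well, and imputation has little left to do for the primary count.

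**3. What differential miscounting would do.** Let the true mean count be μ in both arms, and let directors omit a fraction k₁ of sick days in the Kneipp arm and k₀ in the control arm. The apparent rate ratio is

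μ(1 − k₁) / μ(1 − k₀) = (1 − k₁) / (1 − k₀).

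The documents give no omission rates, so the k values are assumptions:

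- k₁ = 0.05, k₀ = 0: 0.95 / 1 = 0.95
- k₁ = 0.10, k₀ = 0: 0.90 / 1 = 0.90
- k₁ = 0.20, k₀ = 0: 0.80 / 1 = 0.80
- k₁ = k₀ = 0.10: 0.90 / 0.90 = 1.00

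Only a difference between arms matters. This shows how the error would carry through. It is not evidence that the error is likely.

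**The case against.** The strongest reply is that this argues from silence. The article is a condensed text, a separate analysis plan may exist, and imputation variables and agreement tables normally belong there. That stands in part. The imputation variables are unstated, not restricted, so a reader who infers that the caregiver count is excluded, or that double recording can never help recover missing counts, goes beyond the text. It does not answer the ITT rule, which is a positive statement, or the Discussion's reliance on a safeguard that section 2.8 leaves without a stated use.

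Other points on that side:

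- **Site visits.** Section 2.9 provides regular visits to all facilities to secure complete documentation. This makes a missing return less likely and may catch omissions, so it would be wrong to say that nothing guards against them. It is a conduct measure and does not replace a planned analysis.
- **Independence.** Sick days reported to the kindergarten may originate with the parents. The two records may then share a source, and caregivers are also unblinded. This limits what agreement can prove.
- **Certification.** A reader might infer that facilities seeking Kneipp certification would under-count in the Kneipp arm. Table 1 makes seeking certification an entry condition for every kindergarten, so it does not by itself imply a difference between arms.
- **Gain in precision.** It is tempting to put a number on the effective sample gained from the caregiver count. The documents give no correlation between the records, baseline sick days are already in the model, and children who drop out may lack both records. No figure is supported.
- **Timing of returns.** The Abstract's weekly collection can look inconsistent with section 2.1, where directors "report them after completion of each 6-week data collection period". The two are compatible: absences can be recorded through the six weeks and returned once.

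**Conclusion.** The point holds in a limited form. Choosing one source as primary is sound, and the kindergarten report is a reasonable choice. What needs changing is that ITT membership depends on that report, and that the second record, on which the Discussion relies for internal validity, has no stated part in any analysis of absence.

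The consequence that follows from the text alone is the exclusion of children, or of whole clusters, for whom no kindergarten report exists. How many this would affect cannot be known from the documents. The possible bias from differential counting is likewise unquantified. The ratios of 0.95 to 0.80 rest wholly on assumed one-sided omission of 5% to 20%. This is a worthwhile and inexpensive improvement to section 2.8. It does not show that the planned primary result would be wrong.

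**What to change.** In section 2.8:

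1. Keep the kindergarten count as the primary outcome.
2. Define the ITT set as all enrolled children in randomized kindergartens, whether or not a kindergarten report is available. Without this step, the next one cannot retain children whose director made no return.
3. Include the caregiver sick-day count from the same six-week window as an auxiliary variable in the multiple imputation.
4. Repeat the primary negative binomial model on the caregiver count as a named sensitivity analysis.
5. Report the kindergarten-minus-caregiver difference by arm and period.

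The cost is a few lines of text and two short additional outputs. Both records are already being collected, and directors need make no more frequent returns.

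The limits should be stated with the change. Caregiver counts will be incomplete, are unblinded, and may not be independent of the kindergarten record. A difference by arm therefore flags a problem without showing which record is wrong. Where a whole kindergarten made no return, the imputation must assume that its two records would have been related as they are elsewhere.

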### Eligibility criteria

2.2

Eligibility crite shown in Table 1.

**Table 1 tab1:** Eligibility criteria.

	Inclusion criteria	Exclusion criteria
Kindergartens	Berlin kindergartens seeking certification as Kneipp daycare facilities with Kneipp-Bund e.V. Interested in participating in associated training via Sebastian Kneipp Academy. Willingness to engage in pair-randomized group assignment. Must provide pedagogical staff for training as Kneipp educators in autumn 2022 or 2023/24. Implementation of Kneipp concept immediately after training.	Kindergartens already implementing holistic health concepts (e.g., Kneipp, anthroposophical). Staff restricted from participating in training. Facilities unsuitable for implementing the Kneipp concept. Daycare center involved in another study preventing participation in this one.
Educators	Healthy educators, regardless of gender Working in the participating facilities 18–65 years of age Informed consent available	Serious chronic or acute illnesses inhibiting participation. Not speaking or understanding German
Caregivers	Caregivers, regardless of gender 18 years and older At least one child in a participating daycare center included in the study. Informed consent available	Serious chronic or acute illness preventing participation in the data collection. Not speaking or understanding German at the appropriate level for reading and completing study information
Children	Healthy children, regardless of gender 2–6 years Care in the participating kindergartens during study period Consent of the caregivers	Serious chronic or acute illness Not speaking or understanding German Age under 2y/o

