### Sample size

2.5

The sample size selection was formed by a preceding non-randomized controlled study (8) which focused on kindergarten sick days as a primary outcome. The study employed a Chi2-Test (categorizing kindergarten sick days as yes/no), revealing an effect size of *ω* (omega) = 0.41, equivalent to a Cohen’s *d* = 0.66 (8). Recognizing the non-randomized nature of the prior trial, the effect size was conservatively adjusted in half to φ (phi) = 0.205. With standard parameters set at *α* (alpha) = 0.05 (indicating a 5% probability of error in two-sided testing for differences), a power of 80% (*β* (beta) = 0.20), and accounting for an estimated dropout rate of approximately 20%, the optimal sample size for the current study was determined to be 240 child participants. The number of recruited matched kindergarten pairs will be based on the total calculated sample size.

Using a sampling strategy of maximum variation, semi-structured qualitative expert interviews will be planned with up to 15 kindergarten educators in the intervention facilities, while two focused ethnography observations will be each of the intervention kindergartens.

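### Age at baseline is left out of the primary sick-day model: adding it is a free, minor gain in precision and protection against chance imbalance, not a repair of bias

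*Protocol article*

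**What the plan says.** **Primary model (2.8 Statistical methods).** A negative binomial regression of sick days: "This model will include the group (Kneipp vs. Control) and the number of sick days at baseline as predictors". Kindergarten identifiers are also brought in, to see whether there are cluster effects. No other covariate is named.

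**Use of age elsewhere (2.8).** The groups are compared on CCQ scores by an independent t-test, without age. A separate ANOVA looks at whether the group effect differs by sex and age: "This model will include the main effects of group, sex, and age, as well as their interactions". CCQ scores are also correlated with age.

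**Population (2.2, Table 1).** "Healthy children, regardless of gender 2–6 years".

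**Matching (2.6, and similarly 2.3).** "kindergartens with a similar socio-economic level will be match-paired according to statistical demographic analysis of locations in Berlin". The age mix of the children is not a matching variable. Allocation is randomised within pairs.

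**Size (2.5).** The total "was determined to be 240 child participants". The number of kindergarten pairs is not given as a figure.

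**The concern.** Frequency of illness may well differ between a 2-year-old and a 6-year-old, although the document does not say so. With few kindergartens, and pairs formed without regard to age, the arms of the one trial that is run could differ in mean age. If sick days depend on age, part of such a gap would pass into the estimated group effect, because a 6-week count of sick days is a noisy measure of a child's tendency to fall ill and cannot stand in fully for age. Precision would also be lost in the only confirmatory test. Age must be known to apply the eligibility criteria and to run the planned CCQ analyses, so the information is left unused where it would help most.

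**Working it through.** **1. The plan's own sample size.** Inputs from section 2.5: alpha 0.05 ("indicating a 5% probability of error in two-sided testing for differences"), power 80%, and "the effect size was conservatively adjusted in half to φ (phi) = 0.205", with about 20% dropout.

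N = (1.960 + 0.842)² / 0.205² = 186.8, so 187 children. With dropout, 187 / 0.80 = 234, within 3% of the stated 240. The formula has no covariate term, so adding age does not change N. After 20% dropout, 240 × 0.80 = 192 children are analysed.

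**2. How large a chance age gap is likely?** Assumptions, none from the document: age SD 1.15 years, age intracluster correlation (ICC) 0.05–0.10, J = 4–8 kindergartens per arm, m = 192/(2J) children each.

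SE of the difference in mean age = √[2 × SD² × (ICC + (1 − ICC)/m) / J]

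- J = 4, m = 24, ICC 0.10: √[2 × 1.3225 × 0.1375 / 4] = 0.30 years.
- J = 8, m = 12, ICC 0.05: √[2 × 1.3225 × 0.1292 / 8] = 0.21 years.

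A 0.5-year gap is therefore 1.7 to 2.4 SEs, with a two-sided probability of about 10% to 2%. Half of that is in the direction that favours Kneipp. If age clusters more strongly (ICC 0.2, four pairs), the simulated SD is 0.36 years, the gap is 0.5/0.36 = 1.4 SDs, and the probability is about 16%.

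**3. What a 0.5-year gap does, simulation A.** Assumptions: rate falling 10% or 20% per year of age, mean 3 days per window, gamma frailty of shape 2, no true effect.

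- Without baseline adjustment: 0.90^0.5 = 0.95 and 0.80^0.5 = 0.89.
- With the plan's two predictors: about 0.99 and 0.95.
- With age added: within 0.01 of 1.00.

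On these figures baseline sick days remove 1 − ln 0.95 / ln 0.894 = 54% of the log shift at 20% per year, and about 81% at 10%. A repeat with 200,000 children per arm gave 0.98 and 0.96, so about 58% and 65% removed.

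**4. Repeated randomisation, simulation B.** Assumptions: 4, 6 or 8 pairs, 192 children, age ICC 0, 0.1 or 0.2, age effect −0.1 or −0.2 per year on the log scale, mean 3 days, child-level log SD 0.6, dispersion k = 1.5, no true effect, 600 runs in each of 18 scenarios. Models were fitted at child level.

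| | Group + baseline | Group + baseline + age |
|---|---|---|
| Mean log rate ratio | −0.011 to 0.013 | −0.012 to 0.011 |
| SD of log rate ratio | 0.169–0.199 | 0.169–0.190 |
| False-positive rate | 4.3–7.8% | 3.7–6.7% |

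The Monte Carlo SE of a 5% rate is √(0.05 × 0.95 / 600) = 0.9 points. The 7.8% arises with four pairs, ICC 0.2 and effect −0.2. In that scenario the rate is 6.0% with age added and 5.3% with a test on kindergarten-level values. The largest clear fall in SD is there too: 0.199 to 0.189, or 5%. In many scenarios the SD does not change.

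**5. Shift per year of age gap in simulation B, baseline sick days in the model.** The log rate ratio moves by 0 to −0.11 (effect −0.1) or −0.09 to −0.20 (effect −0.2). Much of that spread is simulation noise: at ICC 0 the SE of a slope is about 0.18 / (0.15 × √600) = 0.05. The means over nine scenarios are −0.071 and −0.148, so baseline removes about 29% and 26% here, less than in A. For a 0.5-year gap:

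- mean slopes: exp(−0.5 × 0.071) = 0.97 and exp(−0.5 × 0.148) = 0.93;
- steepest slope: exp(−0.5 × 0.198) = 0.91, in a scenario where the SD of the gap is only 0.17 years;
- four pairs, ICC 0.2, where such a gap is more likely: exp(−0.5 × 0.178) = 0.91.

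A more typical gap of 0.15–0.3 years, with slopes of 0 to −0.20, moves the rate ratio by 0 to 6%.

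**The case against.** The strongest reply is that nothing in the primary model is wrong. Adjusting for the baseline value of the outcome is a standard and valid choice. Kindergartens are randomised within pairs, so an age gap is sampling variation that the test already allows for, and the simulated error rates bear this out. This stands.

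A reader might infer that the omission lets a difference in age be mistaken for a Kneipp effect, that is, confounding. The documents do not support that reading. The mean log rate ratio is about zero with or without age. The year between windows ages both arms equally. The model does not ignore age altogether, since baseline sick days carry part of it.

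A reader might also infer that the plan contradicts itself by adjusting CCQ scores for age but not sick days. It does not. The CCQ group comparison is an unadjusted t-test, and the ANOVA looks for effect modification. Nowhere does the plan state that age predicts sick days.

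Two qualifications keep the point alive. Reliance on randomisation presumes that clustering is modelled, whereas section 2.8 uses the kindergarten identifiers only to find out whether cluster effects exist. It also presumes that the allocated kindergartens stay, whereas section 2.3 replaces those that decline because of their allocation. Neither passage shows that an age difference will arise.

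Finally, an article may leave extra covariates to an analysis plan that is not shown. If that plan already includes age, only the wording needs aligning. The article does, however, list the predictors of its confirmatory model.

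**Conclusion.** The point holds as a minor, free improvement. The primary model omits an inexpensive baseline covariate that matching does not balance. Its absence causes no systematic bias and no material inflation of the false-positive rate when clustering is modelled. The gain from adding it is an SD lower by up to about 5%, often by nothing, and protection of the single realised estimate against an unlucky age split. For a 0.5-year gap the shift is to a rate ratio of about 0.95–0.99 in simulation A and roughly 0.9 at the extreme of simulation B. That compares with an SD of the log rate ratio of 0.17–0.20.

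Every one of these sizes rests on assumed values for the age effect, the clustering of age and the number of pairs, because the document gives none of them. If sick days do not vary with age between 2 and 6 years, there is nothing to gain, and almost nothing is lost by including the term.

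**What to change.** In section 2.8, name the child's age at baseline (continuous, in years) as a covariate in the primary negative binomial model, alongside group, baseline sick days and the kindergarten term. Keep the model without age as a sensitivity analysis. Adding sex is optional.

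The cost is one sentence of protocol or analysis-plan wording and one model term. The sample size does not change, and no data are needed beyond those that eligibility and the CCQ analyses already require. It should be settled before outcome data are examined: in an open-label trial, adding age only after an imbalance has been seen would look data-driven.
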